### 2.9 Data analysis

We will use factorial design mixed-effects models to compare questionnaire battery scores between experimental groups and the control across measurements. In addition, we will perform an interrupted time series analysis to compare the longitudinal effects of the introduction of different types of interventions on longitudinal EMA outcomes.

We will include participants who complete at least 21 EMA assessments spread across the intervention testing period of 5 weeks. Furthermore, for the 6-month follow-up intervention effects retention analysis, we will include participants who complete at least three EMA assessments within the follow-up period. Moreover, in each intervention group, we will retain participants who log onto the app and use the long-term and short-term self-guided intervention modules at least four times and once, respectively, defined as minimal therapeutic exposure. Finally, for the secondary outcome analysis, we will include participants who complete the baseline and at least one follow-up assessment.

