**Methods:**

The 13-armed randomized controlled trial aimed to assess the effectiveness of a mobile app-based self-guided psychological intervention delivered *via* a smartphone app (*Nałogometr*) in reducing craving and lapse risk in problematic alcohol or stimulants use. Participant recruitment and data collection will be performed from June 2022 to September 2022. The 4-week mobile intervention program will include short-term and long-term intervention modules based mainly on mindfulness and cognitive-behavioral therapy. Intervention effectiveness assessment will include Ecological Momentary Assessment. That is, we will collect longitudinal data on a set of characteristics of day-to-day functioning. The primary outcomes will include a self-reported number of lapses and addiction craving level. In contrast, the secondary outcomes will be the severity of problematic substance use, anxiety and depression scores, and life satisfaction scores.

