### 2.3 Sample size calculation

To determine the sample size, a simulation-based power analysis was performed. For the simulation, we assumed a linear mixed-effects model (with random participant-level intercepts), 21 data points (EMA entries) per participant. Based on the results of previous substance use reduction mobile intervention studies [for a review, see Staiger et al. (38)], small effect size of the treatment, i.e., introducing an intervention, was also assumed in the simulation. This analysis suggested that a minimum sample size of 650 participants will be necessary to achieve 80% power of detecting a treatment effect. Due to the nature of the study, i.e., a nationwide study of problematic substance (alcohol and stimulants) use, our sampling strategy has been designed. to maximize the demographic diversity of the resulting sample, particularly with respect to demographic characteristics (e.g., gender, age, geographic and socioeconomic setting) within each addiction profile.

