### 2.5 Procedure

The study will be conducted *via* the mobile application *Nałogometr*, a proprietary custom-design mobile app available from Google Play or the App Store. The download and onboarding process in the app will be used as baseline data in the study. Upon first use, the app will automatically navigate the participant through necessary permissions and consent about the collection of different types of data. After logging in, participants will be asked to complete a baseline onboarding questionnaire that collects demographic information and their substance use or behavioral habits.

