### 2.6 Randomization

Randomization will be applied using an automated balancing algorithm. The algorithm will aim to partition participants into groups based on the initial onboarding assessment to make the resulting groups as balanced as possible concerning the characteristics outlined in the study design section, i.e., (1) primary addiction type; (2) participation in addiction-related therapy; (3) gender; (4) age; (5) addiction severity; (6) abstinence duration. Following randomization, participants in groups 1–12 will receive access to the intervention modules following a 5-day delay. In conditions 1:10, participants get access to the short-term intervention module and one type of long-term intervention. In condition 11, participants get access to the short-term intervention module and all long-term interventions. In condition 12, participants get access only to the short-term intervention module.

Participants in the waitlist control group will be able to access all intervention materials 5 weeks following study enrollment (see Figure 1).

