### 2.8 Measures

Sociodemographic data include gender, age, and place of residence. Substance use-related questions include frequency of use, lifetime use, treatment seeking, and abstinence period (see Supplementary Tables 1, 2). The study includes EMA (three times a day) assessing several variables: craving, lapses, mood, arousal, pressure, anxiety, procrastination, loneliness, tiredness, anger, hunger, and uncertainty (see Supplementary Table 3).

Moreover, the questionnaire assessment will occur three times during the study period (see Table 2).

**TABLE 2 T2:** Timeline of the questionnaire assessment.

Assessment instrument	Baseline (week 1)	Follow-up (week 5)	Follow-up (month 6)
Socio-demographic questions	*x*		
Substances use-related measures			
Psychological dependence (SDS)	*x*	*x*	*x*
Alcohol (AUDIT)	*x*	*x*	*x*
Stimulants (DUDIT)	*x*	*x*	*x*
Psychopathological symptoms measures			
Depression and anxiety (HADS)	*x*	*x*	*x*
Psychological functioning measures			
Sensation seeking (BSSS)	*x*	*x*	*x*
Emotion regulation (DERS)	*x*	*x*	*x*
Impulsivity (UPPS-P)	*x*	*x*	*x*
Coping with stress (Mini-COPE)	*x*	*x*	*x*
Life satisfaction (SWLS)	*x*	*x*	*x*

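### As most naturally read, the questionnaire model measures arm effects as change from baseline, which is valid but less precise than adjusting for the baseline score already collected

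*Protocol article*

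**What the plan says.** Section 2.9 of the protocol article gives the questionnaire analysis in one sentence: "factorial design mixed-effects models to compare questionnaire battery scores between experimental groups and the control across measurements". It names no contrast, no baseline covariate and no constraint on the baseline means.

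Section 2.8 says that "the questionnaire assessment will occur three times during the study period". Table 2 gives the occasions as baseline (week 1), week 5 and month 6, and schedules SDS, AUDIT, DUDIT, HADS and SWLS at all three.

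On who is analysed, section 2.9 says: "for the secondary outcome analysis, we will include participants who complete the baseline and at least one follow-up assessment". Everyone in this analysis therefore has a baseline score. The same paragraph also keeps, within each intervention group, only participants who reached a minimum use of the modules. It does not limit that condition to the EMA outcomes.

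Section 2.6 opens the modules 5 days after randomisation in groups 1 to 12. It gives the waitlist all materials 5 weeks after enrolment.

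**The concern.** Table 2 makes baseline one of the measurements, so a factorial group-by-measurement model ordinarily gives each arm its own baseline mean. The effect of an arm against the waitlist is then the interaction: change from baseline in one arm minus change in the other. This contrast carries in full whatever chance difference the two arms had at baseline.

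Randomisation makes the true baseline means equal, and an analysis that uses this fact estimates the same effect with less noise. The usual ways are to enter the baseline score as a covariate or to fit one baseline mean common to all arms.

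Precision is scarce here. The trial has 13 arms and a minimum of 650 participants, and section 2.3 sizes it on EMA entries, not on the questionnaires. Each arm-versus-waitlist comparison of a secondary outcome may rest on about 50 people per arm, before dropout.

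**Working it through.** **The plan's own figure.** Section 2.3 states that "a minimum sample size of 650 participants will be necessary to achieve 80% power of detecting a treatment effect". It gives no figure for the questionnaire model. It also leaves out the numerical effect size, the within-person correlation and the significance level, so 650 can be neither reproduced nor refuted. The check below uses it only to set a number per arm.

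**Inputs**
- Arms: 13 (Abstract, Methods). Total: 650 (section 2.3). With equal allocation, which is assumed because no ratio is stated, n = 650/13 = 50 per arm.
- Assumed: complete data, SD of 1 at each occasion, the same correlation r between any two occasions, two-sided 5% test, 80% power, normal approximation. The documents do not give r, so a range is shown.

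**Formulas for the week-5 contrast of one arm with the waitlist**
- Change from baseline (free baseline mean per arm): variance = 2(1 − r) × 2/n
- Adjusted for baseline (covariate or common baseline mean): variance = (1 − r²) × 2/n
- Ratio, adjusted to change: (1 − r²) / [2(1 − r)] = (1 + r)/2
- Detectable effect at 80% power: (1.960 + 0.842) × SE

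**Example, r = 0.5.** Change: 2 × 0.5 × 0.04 = 0.040, SE 0.200, detectable effect 0.560 SD. Adjusted: 0.75 × 0.04 = 0.030, SE 0.173, detectable effect 0.485 SD.

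| r | SE, change | SE, adjusted | Variance ratio (1+r)/2 | Detectable effect, change → adjusted (SD) |
|---|---|---|---|---|
| 0.3 | 0.237 | 0.191 | 0.65 | 0.663 → 0.535 |
| 0.5 | 0.200 | 0.173 | 0.75 | 0.560 → 0.485 |
| 0.7 | 0.155 | 0.143 | 0.85 | 0.434 → 0.400 |
| 0.8 | 0.126 | 0.120 | 0.90 | 0.354 → 0.336 |
| 0.9 | 0.089 | 0.087 | 0.95 | 0.251 → 0.244 |

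An exact generalised least squares calculation with three occasions gives the same variances. In 10,000 simulated trials per setting, the ratio of change variance to adjusted variance was 1.34, 1.17 and 1.10 at r = 0.5, 0.7 and 0.8. The formula 2/(1+r) gives 1.33, 1.18 and 1.11.

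**In terms of power**
- True effect 0.5 SD: 70.5% → 82.3% at r = 0.5, 89.8% → 93.8% at r = 0.7, 97.7% → 98.6% at r = 0.8.
- True effect 0.2 SD (assumed as a value for the small effect in section 2.3): 17% → 21% at r = 0.5, 25% → 29% at r = 0.7.

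Below r = 0.5 the factor 2(1 − r) exceeds 1, so the change contrast is then less precise than comparing week-5 scores with no use of baseline.

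**The case against.** **The sentence is condensed.** Free baseline means in each arm are inferred, not stated. A model with a common baseline mean would also fit the wording, and such detail is often left to a fuller plan. This stands, and the point is therefore put as the most natural reading. It still rests on what the article does say: the model type, the comparison, and baseline as one of the measurements.

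**Group-by-time is a valid and common analysis.** This also stands. Under randomisation the contrast is unbiased, and only precision is lost. At r between 0.7 and 0.9 the change contrast has only about 18% to 5% more variance. For an effect of 0.2 SD, power is low either way.

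**Balancing already helps.** Section 2.6 includes addiction severity among the balancing factors. That should reduce chance baseline differences on AUDIT, DUDIT and SDS, but less so on HADS and SWLS.

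**Adjustment is not free in a filtered set.** This is the strongest objection. The module-use condition applies to intervention groups and cannot apply to the waitlist before week 5. If people who engage differ at baseline, the analysed arms no longer share a true baseline mean. As an illustration with assumed values, a lasting difference of 0.2 SD with r = 0.5 would bias the adjusted contrast by (1 − 0.5) × 0.2 = 0.1 SD, whereas the change contrast would cancel it. Neither method is protected in general against such selection. The fix must therefore be tied to a set without that filter.

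**A stronger reading to avoid.** A reader might take the comparison across measurements to be a group main effect averaged over all three occasions. A true effect would then be diluted by a time point at which none can exist. The article does not say this. In a repeated-measures factorial model the phrase ordinarily means group by time, so that dilution should not be attributed to the plan.

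**Conclusion.** The point holds as a matter of efficiency in the secondary outcomes. As most naturally read, section 2.9 compares changes from baseline and does not adjust for a score that every analysed participant has. Adjustment would bring the variance of the week-5 contrast to (1+r)/2 of its present value. Using the change contrast costs the equivalent of one third more participants at r = 0.5 (1/0.75 = 1.33), about 18% more at r = 0.7 (1/0.85 = 1.18) and about 5% more at r = 0.9 (1/0.95 = 1.05). The loss is therefore material at r of 0.5 or below and modest at high r.

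These sizes assume 50 per arm, complete data and equal correlations, with r unknown. The gain from adjustment also requires an analysis set that keeps the randomised comparison.

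Two further inferences are not supported. The plan is not shown to be biased or self-contradictory here. The primary EMA outcomes, which section 2.9 assigns to an interrupted time series analysis, are not affected.

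**What to change.** In section 2.9, and in the pre-registration if it says the same, state that:

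1. Questionnaire scores at week 5 and month 6 are the outcomes in the mixed model, with the same instrument's baseline score as a covariate (or one baseline mean common to all 13 arms).
2. The arm-versus-waitlist effect is the week-5 contrast, because the waitlist gains access to all materials at 5 weeks and month 6 is no longer a comparison with an untreated group.
3. The analysis uses participants as randomised who have a baseline and at least one follow-up score, without the module-use filter.
4. Baseline scores are recorded before the modules open. Table 2 dates baseline to week 1, while access begins after 5 days.

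The cost is a few lines of text, with no new data and no extra participants. There is one small downside: if a set filtered on module use is also analysed, baseline adjustment there is not protected against differences that the filter creates between arms. That analysis should be labelled accordingly.

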Ecological Momentary Assessment (EMA) involves the repeated sampling of subjects’ current behaviors and experiences in real time in natural environments. EMA holds the unique promise to advance the science and practice of clinical psychology. Surveys were a traditional tool in research on addictions, but they are only point measurements that do not capture the dynamics of changes in behavior. EMA was used in tobacco and alcohol use disorders and relatively less often in heroin and cocaine research regarding both in-treatment and recovery patients (27). In methamphetamine- or cocaine-dependent participants, studies with EMA assessed stress and the cognitive, affective, and motivational factors on drug craving (28–30). EMA used in self-monitoring was effective and reliable in treating and assessing eating disorder urges (31). EMA and self-monitoring methods support behavior change and self-management by increasing the awareness of addictive behaviors and triggers, goal progress tracking, self-rewards, reminders, reinforcement, and personal feedback (32).

Due to the high risk of relapse in addiction (33), mobile health (mHealth) interventions could be a valuable tool for enhancing the post-therapeutic effects after treatment (34). The mHealth interventions delivered through smartphone apps are gaining popularity; however, the evidence for their effectiveness often remains unsolved (35). With over 300,0000 health applications available (36), a small number have been clinically tested before entering the market (37). Currently, there are no evidence-based mobile apps in Poland that effectively reduce craving and lapse risk in substance use disorders. The present study aims to test the effectiveness of mobile app-based self-guided psychological intervention delivered *via* a smartphone app (*Nałogometr*) involving EMA in reducing craving, lapse risk, and substance use (alcohol, stimulants).

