#### 2.8.1 Primary outcome

The primary outcomes of interest are the self-reported lapses (number of lapses reported in daily EMA) and addiction craving (intensity of the urge to use a given substance at the moment of completing the assessment) (see Supplementary Table 3).

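### For the primary EMA outcomes the plan states no contrast with the waitlist, so whether any intervention beats none has no stated analysis

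*Protocol article*

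**What the plan says.** Section 2.8.1 defines the primary outcomes: "The primary outcomes of interest are the self-reported lapses (number of lapses reported in daily EMA) and addiction craving". Both are EMA measures. Section 2.9 then gives one analysis per outcome family:

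- Questionnaire scores, which include every secondary outcome in 2.8.2: "We will use factorial design mixed-effects models to compare questionnaire battery scores between experimental groups and the control across measurements".
- EMA outcomes, which include both primary outcomes: an "interrupted time series analysis to compare the longitudinal effects of the introduction of different types of interventions on longitudinal EMA outcomes".

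The design facts that bear on this are in 2.6. For the active arms, "participants in groups 1–12 will receive access to the intervention modules following a 5-day delay". For the control, "Participants in the waitlist control group will be able to access all intervention materials 5 weeks following study enrollment". One arm isolates the short-term component: "In condition 12, participants get access only to the short-term intervention module". EMA three times a day is described for participants without distinction by arm. The Discussion says the trial is to find out both whether the interventions work and which of them do.

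**The concern.** The sentence on the secondary outcomes names the control and the sentence on the primary outcomes does not. Comparing intervention types answers which of them does better. It does not answer whether an intervention does better than none.

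If that second question were answered from the change at day 5 inside each active arm, the module effect could not be separated from whatever else changes with time on study. The document gives reasons to expect such change. Access opens at the same day in groups 1 to 12, so it coincides with a fixed time since enrolment. The Introduction says that "EMA and self-monitoring methods support behavior change and self-management by increasing the awareness of addictive behaviors", and EMA starts before the modules do. The weekly report (2.7.1.2) covers seven days, so the first full report falls after day 5, on the same side of the break as the modules.

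**Working it through.** **1. What each contrast can identify.** Let D be the mean change around day 5 that would occur without any module, S the effect of the short-term module, and L_k what long-term module k adds to it. Randomisation makes D the same in all arms in expectation.

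| Arm | Change at day 5 |
|---|---|
| Waitlist | D |
| Condition 12 | D + S |
| Conditions 1 to 10 | D + S + L_k |
| Condition 11 | D + S + L_all |

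- Type k minus type j: L_k − L_j. D cancels.
- Type k minus condition 12: L_k. D cancels.
- Condition 12 minus waitlist: S. Type k minus waitlist: S + L_k. D cancels.
- Change within arm k: D + S + L_k. D stays in.

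So S, and any package S + L_k, needs the waitlist or an assumption about D. Estimating D from the pre-period rests on few data: at most 3 × 5 = 15 prompts. A participant at the 21-entry minimum, spread evenly over 35 days, supplies about 21 × 5/35 = 3.

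**2. Does the sample size show which contrast was meant?** Section 2.3 gives 650 participants, 80% power, 21 entries and a small effect. It gives no numerical effect size, ICC, alpha or contrast, so 650 cannot be reproduced. Assume two-sided alpha 0.05, d = 0.3 and ICC 0.5. The SD of a participant mean is √(0.5 + 0.5/21) = 0.724, and (2.80 × 0.724/0.3)² ≈ 45.7.

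- All 12 active arms against the waitlist: 45.7 × (1 + 1/12) = 49.5, so 50 per arm and 13 × 50 = 650.
- Two equal groups: 2 × 45.7 = 91.4, so 92 per group and 184 in total.
- Pairwise between 13 arms: 13 × 92 = 1,196.

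The first variant matches, but so nearly does d = 0.2 with ICC 0.2 (663). Over d = 0.1 to 0.3 and ICC 0.2 to 0.7 the variants run from 84 to 14,586. The figure does not settle the contrast.

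**3. How much D could matter in a within-arm reading.** All inputs are assumed: zero module effect, 35 days, one entry a day, break at day 5, 50 per arm (650/13, equal allocation), total SD 1, ICC 0.5, 1,000 simulated trials, two-sided 5%.

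| Shared drift | Single arm, before/after step | Single arm with pre-trend: level / slope | Type vs type, step | Type vs waitlist, step |
|---|---|---|---|---|
| None | 5% | 6% / 7% | 5% | 4% |
| Linear, −0.2 SD | 56% | 5% / 6% | 5% | 6% |
| Curved, −0.2 SD | 73% | 6% / 12% | 5% | 4% |
| Curved, −0.3 SD | 99% | 7% / 15% | 6% | 6% |

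Hand check of the linear row: the post-period mean day is 19.5 and the pre-period mean day 2, so the spurious step is 17.5 × 0.2/34 = 0.103 SD. Its SE is √(0.5 × (1/30 + 1/5)/50) = 0.048, z = 2.13, and the rejection rate is Φ(2.13 − 1.96) = 0.57, against 56% simulated.

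**4. What the waitlist contrast costs.** With 3 entries before and 18 after day 5 and ICC 0.5, the SD of a participant's change is √(0.5 × (1/3 + 1/18)) = 0.441. For a true effect of 0.2 SD:

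- One arm before/after: SE 0.441 × √(1/50) = 0.062, power 0.89, but for D + S + L_k.
- One arm against the waitlist: SE 0.441 × √(2/50) = 0.088, power 0.62.
- 12 arms pooled (600) against the waitlist (50): SE 0.441 × √(1/50 + 1/600) = 0.065, power 0.87.

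**The case against.** A reader might infer that the waitlist is discarded for the primary outcomes, or that time trends will be reported as module effects. The document supports neither.

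- The rule of at least 21 EMA entries is not restricted by arm, whereas the minimum-exposure rule is limited to intervention groups. That fits an analysis set that also holds the waitlist.
- The waitlist's five weeks without modules match the five-week testing period. An uninterrupted concurrent series is what a controlled interrupted time series uses, so the waitlist fits this method naturally.
- The sentence says the types are to be compared. Drift shared by randomised arms cancels in that comparison, and step 3 shows about 5% false positives.
- Condition 12 is a randomised comparator for each long-term module, and the Discussion stresses which long-term interventions work best.
- This is a condensed article of a pre-registered study. Trend terms and contrast coding may stand elsewhere.

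The first four points stand in full. The last stands for model detail. It does not fully cover the comparator: the article names one for the secondary outcomes, and the contrast it gives for the primary outcomes cannot answer half of the stated aim.

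**Conclusion.** The point holds as a gap in the stated primary contrast, not as a demonstrated bias. The stated comparison can rank types, and with condition 12 as reference it can estimate what each long-term module adds. Nothing stated estimates the short-term module, or any package, against no intervention.

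The consequence is conditional. If that question were answered from within-arm change, the false-positive rate would range from near nominal (pre-trend modelled, linear drift) to almost certain (no trend term, curved drift of 0.3 SD). These rates depend on the assumed drift, ICC, arm size and entry pattern, and are not properties of the analysis as written. The cancelling of D assumes that the waitlist has the same EMA and weekly feedback as the other arms, as the undifferentiated description suggests, and that the arms are compared as randomised. The exposure rule that applies only to intervention groups is a separate threat to the latter.

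**What to change.** In 2.9, state a controlled interrupted time series, fitted as a mixed model, for both craving and lapses:

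- Apply the day-5 phase in all 13 arms, including the waitlist.
- Include a time trend common to all arms.
- Make the arm-by-phase contrasts against the concurrent waitlist, up to week 5, the primary estimates.
- Keep the comparisons between types and with condition 12 for the question of which module works best.
- Report within-arm before/after changes as descriptive only.

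This is a change of wording before analysis. The EMA schedule as described already covers the waitlist, so no new data are needed. The price is precision: the standard error is √2 = 1.41 times that of an uncontrolled before/after test for one arm against the waitlist at equal size. For all active arms pooled it is √13 = 3.6 times that of an uncontrolled test in 600. The uncontrolled test is narrower only because it assumes D away.

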**FIGURE 1 F1:**
[figure not shown]
Participant flow chart.

The study will take place from June 2022 until September 2022, with ongoing participant recruitment. The study includes ecological momentary assessment (EMA), assessing several variables important linked to lapse risk. Participants will be asked three times daily to answer questions about their mood, psychological and physiological state, craving, and if lapses occur. EMA will be administered daily between 6 a.m. and 12 a.m (morning EMA) and between 4 p.m. and 10 p.m. (evening EMA). Participants can select a specific time for assessment delivery that best suits their schedule and needs. When prompted to complete the EMA, participants will have the time to complete it until the next scheduled. Assessments are designed to take less than 2 min to complete. In addition, participants will be able to initiate assessments themselves to not skip any measurements for the day.

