##### 2.7.1.3 Self-guided psychological intervention modules

Two main self-guided intervention modules were created for a mobile app: (1) short-term self-guided intervention module and (2) long-term self-guided intervention module (Table 1 and Figure 2). The delivery of these interventions will be initiated 5 days following study enrollment.

**TABLE 1 T1:** Intervention modules in the mobile app.

Intervention modules	Description
Short-term interventions	This module consists of audio-guided sessions on gratitude, auto-empathy, thoughts management, and relaxation. Moreover, they are based on breath relaxation exercises, craving management, and motivation to change.

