## 3 Discussion

This study protocol describes a randomized controlled trial designed to determine the effectiveness of self-guided psychological intervention modules delivered *via* a smartphone app (*Nałogometr*). We aim to examine whether and which interventions can effectively reduce craving and lapse risk in problematic alcohol or stimulant use. The embedded trial and analysis will evaluate the effectiveness of intervention modules for alcohol or/and stimulants use. In exploratory analyses, we investigate whether user engagement moderates or changes in psychological functioning measures (e.g., sensation seeking, impulsivity, stress coping, emotion regulation) mediate the effectiveness of the interventions. We hope to determine if these interventions delivered through mobile devices can be effective and contribute to future prevention or therapy addiction programs. The wide availability and accessibility of developed interventions are a substantial advantage. Mobile app interventions may reduce treatment barriers by staying anonymous and avoiding stigma and may be especially useful in places where professional help is unavailable (49–52). We plan a 6 months follow-up to conduct a longer-term evaluation and check the sustainability of the potential change in the user’s behavior–it is an essential factor for relapse prevention through the management of craving. Such a complex study of 13 conditions will allow us to understand better which long-term interventions are most effective. We include multiple intervention types to better assess their effectiveness across diverse individuals. One limitation of the present study could be that the participant dropout will be higher than expected based on previous research (53, 54). Due to the lack of personal contact with researchers and no additional incentives, e.g., prizes or monetary remuneration, the commitment to participate throughout the study may be lower, and motivation may decrease over time.

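### The 21-entry rule selects the primary EMA analysis set on behaviour after randomisation, and it does not secure data before and after the modules open

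*Protocol article*

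**What the plan says.** Section 2.9 states: "We will include participants who complete at least 21 EMA assessments spread across the intervention testing period of 5 weeks". It does not define the spread and sets no minimum for any week, or for the time before or after module access. It describes no analysis of all randomised participants. Section 2.8.1 takes both primary outcomes from EMA, and section 2.9 plans an interrupted time series for them.

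Other sections fix the timing:
- Module access, section 2.7.1.3: "The delivery of these interventions will be initiated 5 days following study enrollment".
- Programme length, abstract: "The 4-week mobile intervention program will include short-term and long-term intervention modules".
- Waitlist, section 2.6: its participants "will be able to access all intervention materials 5 weeks following study enrollment".
- EMA frequency, section 2.6 (text after Figure 1): "Participants will be asked three times daily to answer questions about their mood, psychological and physiological state, craving, and if lapses occur". Only a morning and an evening window are then named.
- Extra entries, same place: "participants will be able to initiate assessments themselves to not skip any measurements for the day". Whether these can exceed the daily schedule is not said.

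The Discussion allows that "the commitment to participate throughout the study may be lower, and motivation may decrease over time". Section 2.3 assumes 21 EMA entries per participant and a mixed model with participant-level intercepts in the power simulation.

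**The concern.** Two faults are at issue.

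First, whether a participant reaches 21 entries is known only after allocation. Someone may stop short because of the arm they are in, or because of how they are doing. Restricting the analysis to those who reach the count gives up the balance that randomisation provides, for both primary outcomes. Lapses are seen only where an entry exists, so the filter acts on the same activity that produces the outcome data.

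Second, an interrupted time series compares the course after an intervention starts with the course before it. A single total says nothing about how entries fall on either side of module opening. The rule can keep people with little data on one side and drop people with data across the whole period.

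The planned class of model does not need the floor. Mixed models accept unequal numbers of entries per person.

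**Working it through.** **1. The plan's own figure.** Section 2.3 gives 650 participants from a simulation with 21 entries each. The numerical effect size, alpha, intraclass correlation and contrast are not in the article, so 650 can be neither reproduced nor refuted. The point does not depend on it. The link is only that the 21 assumed for power is also the inclusion threshold.

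**2. The window.** Modules open after 5 days and the programme lasts 4 weeks: 5 + 28 = 33 days, close to the 35 days after which the waitlist gets access. The 5-week window therefore most naturally starts at enrolment and contains 5 days before access and 30 after. This is inferred; section 2.9 does not name the start day.

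**3. When complete logging reaches 21.** Entries before opening = 5 × entries per day; entries still needed = 21 minus that.

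| Entries per day | Possible in 35 days | 21 as share | Day reached | Before opening | After opening |
|---|---|---|---|---|---|
| 3 (stated frequency) | 105 | 20% | 21/3 = 7 | 15 | 6 |
| 2 (windows named) | 70 | 30% | 21/2 = 10.5, so day 11 | 10 | 11 |

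At three a day, 15/21 = 71% of the quota can come before the modules open. If three a day is also the cap, at least 6 entries must come after opening, so nobody who stops by day 5 qualifies.

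**4. Who is dropped.** Four entries a week gives 4 × 5 = 20, one short. About 20 × 30/35 = 17 of these lie after opening. One entry every second day gives 18, also excluded. The break-even is 21/5 = 4.2 entries a week.

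**5. How sharply the rule cuts.** If each of 105 prompts is answered independently with a constant probability (assumed), the binomial probability of at least 21 is 0.10 at 15% completion, 0.54 at 20% and 0.91 at 25%. With 70 prompts the same completion rates give 0.001, 0.03 and 0.20.

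**6. No earlier data at all.** Up to 30 × 3 = 90 entries are possible after opening, so 21 can be met with none in days 1 to 5.

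**7. Can selection create a difference?** The documents give no dropout rates, so this is illustration only. One simulation assumed three prompts a day, 3% stopping per day plus 10 points on a lapse day, and no module effect on lapsing. Mean daily lapse probability was 0.231 in all randomised and 0.201 in those retained. Among those retained it was 0.216 if the extra stopping was removed and 0.188 if it was 20 points. Against 0.201 these are +0.015 and −0.013. The figures also rest on assumed completion and an assumed spread of lapse risk, and the gap nearly vanishes if everyone logs completely until they stop.

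These are differences in level. For pre-to-post change, closer to what the time series estimates, another set of assumed rates gave 0.0125 against 0.0151, a gap of about 0.003, where the levels differed by 0.026. Other assumptions gave gaps in change up to about 0.03, some in the opposite direction.

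**The case against.** The strongest replies are these.

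- **The wording already bars early stoppers.** Entries made only on days 1 to 7 are not, in ordinary reading, spread over five weeks. A reader might infer from the arithmetic that the plan admits people who quit by day 7. The documents do not support that as fact. It needs complete logging at three a day and a loose reading of the spread, and with the two named windows it becomes day 11. Participants in the intervention groups must also meet the module-use minimum of four long-term uses and one short-term use, which leaves a day-7 stopper about two days. What stands is that the phrase has no working definition, so it can be applied either way.
- **No link between lapsing and logging is documented.** A reader might infer that people who lapse stop logging. No section says so. The Discussion ties lower commitment to the lack of personal contact and incentives. The link is plausible, but it is an inference.
- **The time series works on change.** Stable differences between people largely cancel. This is fair, and it rules out quoting a level difference as the bias of the planned analysis. It does not remove bias when stopping depends on how a person fares after the modules open.
- **The threshold is the same in every arm and matches the power assumption.** Both are true. An equal threshold does not protect the comparison if the arms differ in who reaches it, and a planning assumption about data volume is no ground for excluding people.
- **Counting entries before opening is legitimate.** It is, since the time series needs them. The fault is the missing minimum on each side.

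**Conclusion.** The concern holds in this form. Section 2.9 makes entry to the analysis of both primary outcomes depend on a count observed after randomisation, and it describes no analysis of all those randomised. With falling commitment anticipated, the rule can be expected to remove people. Whether this biases the comparison depends on whether the modules alter who keeps logging. The documents settle neither the direction nor the size, so no percentage should be attached to it.

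The second part rests on counting. The rule can be met with as few as 6 entries after opening, or with none before it, while 20 entries spread evenly over five weeks fail. This assumes that the window starts at enrolment, that entries follow the stated schedule and, for the early-completion cases, that the spread is read loosely. The day-7 and day-11 cases show that the rule is loose; they are not a forecast of how many participants will behave so.

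**What to change.** For the primary EMA analysis, replace the 21-entry rule with all randomised participants in their allocated arm, using every available entry in the mixed or time-series model and no minimum count. Report by arm how many contribute no entries, and how many contribute none before or none after opening. Substituting a condition such as at least one entry after day 5 would not cure the fault, because that too is observed after randomisation.

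Keep the 21-entry set as a sensitivity analysis only. Define it by phase, with a stated minimum before and after opening, and apply it identically in all arms, including the waitlist. State the day on which the window starts, and reconcile the three daily assessments with the two named windows.

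The cost is wording in the protocol and the analysis-set definitions; no new data are needed. Sparse participants add some noise, and the estimated effect may be less favourable than among frequent loggers. The change does not abolish missing data: the mixed model still relies on stopping being explained by what was observed, and the sensitivity analyses should say so.
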